## Abstract

Relatives of type 2 diabetic patients are at a high risk of developing type 2 diabetes and should be regarded as target of intervention for diabetes prevention. However, it is usually hard to motivate them to implement preventive lifestyle changes, because of lack of opportunity to take advises from medical professionals, inadequate risk perception, and low priority for preventive behavior. Prevention strategy for them therefore should be highly acceptable and suited for them. The parallel, three-group trial is now being conducted to investigate the effects of genetic counseling and/or a computerized behavioral program on the prevention of type 2 diabetes in that population. The preventive strategies used in this study could provide a novel solution to the numbers of genetically high-risk individuals, if found to be effective. The objective of this paper is to describe the background, protocol, and baseline patient characteristics of the trial.

## 1. Background

The number of patients with type 2 diabetes has rapidly and continuously increased in recent years and has become a global burden. Development and implementation of strategies to prevent type 2 diabetes are therefore urgently required. Identification of a high-risk population is one of the most important steps in the development of effective and efficient prevention strategies. Several risk factors for type 2 diabetes have been identified in epidemiological studies. Obesity is the most common risk factor for type 2 diabetes, and a vast amount of literature has reported on interventions aiming to reduce obesity.

 The effectiveness of lifestyle intervention for diabetes prevention has been confirmed by large, randomized, controlled trials in both Western countries [1–3] and Asian countries [4–7]. The subjects of these studies were at high risk for developing diabetes, being obese, and/or having impaired glucose tolerance. The goal of lifestyle interventions in these studies was mainly weight reduction. All of these studies definitely succeeded in preventing diabetes, while weight reduction patterns differed between Asian and Western countries. Studies in Asian countries showed a preventive effect with a smaller weight reduction (0 to 2.5 kg/year) [6, 7] than those in Western countries (4.2 to 7.0 kg/year) [2, 3]. These results reflect obvious differences in baseline body mass index (BMI) among different regions. The target population in preventive research trials usually has a BMI of ≥30 kg/m^2^ in Western countries and about 25 kg/m^2^ in Asian countries [8]. Recent global epidemiological meta-analysis has shown that BMI is strikingly lower in Asian populations compared with Oceania, Australasia, Europe, and North America [9]. Among developed countries, Japanese males have the lowest mean male BMI (23.5 kg/m^2^) and Japanese females have nearly the lowest mean female BMI (21.4 kg/m^2^) [9]. Moreover, Japanese patients with diabetes characteristically have a relatively low BMI [10]. Focusing on obesity would therefore be a less efficient method of identifying high-risk individuals in Asian countries than in Western countries, and it is necessary to focus on risk factors other than obesity.

Etiologically, type 2 diabetes results from a complicated combination of genetic and environmental factors. Individuals genetically predisposed to type 2 diabetes therefore represent an important target for preventive strategies. Some studies have suggested that the Japanese are genetically predisposed to developing diabetes because they have a higher frequency of some diabetes susceptibility genes than Caucasians [11–13]. A recent study reported a diabetes susceptibility gene specific to lean (BMI <24 kg/m^2^) Japanese people [14]. These findings suggest that genetic considerations are especially important in diabetes prevention strategies for the Japanese.

Family history is a well-known risk factor for type 2 diabetes and has been used to screen high-risk populations [15–17] from both genetic and environmental viewpoint. Offspring of patients with type 2 diabetes have a higher risk of developing the disease since they are likely to share the same genetic predispositions and have similar lifestyle habits as their parents [18]. Individuals with an affected first-degree relative have a 2.3- to 5.5-fold higher risk of developing type 2 diabetes, independent of sex, age, race/ethnicity, BMI, and other demographic characteristics [19]. Family history is thus a useful tool for detecting genetically high-risk populations in this postgenomic era [20, 21].

 Some studies have already revealed positive effects of lifestyle interventions for dietary habits in relatives of diabetic patients [22–24], and of increasing recognition of diabetes risk [25]. These results suggest that intervention for relatives would be effective if delivered in a useful way. However, it is difficult for medical professionals to reach the relatives of patients in both research and clinical settings, because the relatives rarely visit hospitals unless they get ill. One way to contact relatives to offer general genetic counseling and promote preventive behavior is to utilize patient as intermediaries between medical professionals and relatives [26, 27]. Unfortunately, using patients in this role had not been demonstrated to be effective in diabetes. The rates of participation in lifestyle intervention programs offered to relatives through patients have been reported to be disappointingly low (5–13.5%) [24, 28], and advice about lifestyle modification given by patients was reported to have no effect on their offspring's preventive behavior [29].

These results suggest that it is difficult to motivate relatives to implement preventive lifestyle changes, especially through patients. It is therefore essential for diabetes preventive strategies to establish a way to contact relatives directly, in order to provide lifestyle intervention programs and maintain compliance in such programs.

One of the most common opportunities for medical professionals to make contact with the offspring of patients with type 2 diabetes is at the time of a medical checkup. In Japan, employers have a legal obligation to allow their employees an annual health checkup. Additionally, the Japanese Ministry of Health, Labour and Welfare enacted the Specific Health Checkup (SHC) in 2008 that aims to identify individuals at high risk for the development of metabolic syndrome in both employed and nonemployed populations. The SHC is mainly undertaken by municipal governments, who will be penalized by central government if they cannot achieve the target consultation rate (e.g., 65% by 2012). Most of the Japanese population is therefore expected to undergo medical checkups. Subjects are usually asked during the checkup if they have a family history of common diseases such as stroke, cardiovascular disease, infectious disease, lipidemia, or diabetes. Unfortunately, this information about family history has not been fully utilized as a screening tool for implementation of intervention to prevent type 2 diabetes [30, 31]. The current study therefore aims to screen for high-risk individuals using information about family history, and then contact subjects directly to provide preventive intervention.

As mentioned above, it is difficult to motivate the relatives of patients with type 2 diabetes to implement preventive lifestyle changes. For high-risk individuals to become actively involved in prevention, recognition of the risk of acquiring the disease is crucial [32, 33]. Risk education is therefore important as the first step in motivating relatives of patients. Information about disease susceptibility is sometimes a psychological burden for high-risk people, especially those who are genetically predisposed [34]. Genetic risk education should therefore be provided as a component of genetic counseling, which is the medical/psychosocial process that disease predisposed subjects are advised of the consequences, nature, and management of an inherited disorder, even though previous research has shown that such information mainly has a favorable effect on psychological issues [25, 35]. However, genetic counseling often seems to be less feasible in the health checkup setting since it takes more time than usually available at an outpatient clinic. It was therefore essential to develop a counseling tool which enables medical professionals to explain genetic diabetes susceptibility and diabetes prevention quickly and adequately. The authors developed a six-page booklet based on the traditional health belief model [33], which can be utilized for brief genetic counseling including risk education about type 2 diabetes. In the current study, brief genetic counseling by a certified genetic counselor was provided to subjects using the booklet. Then the current study tried to investigate the effect of that genetic counseling on participant's compliance to the lifestyle intervention.

To maintain compliance with lifestyle interventions, the interventions should be easily available. It is particularly difficult to motivate the offspring of type 2 diabetic patients to receive preventive intervention, as they are generally healthy and have other demands on their time. Previous research has indicated that healthy subjects prefer correspondence format programs to face-to-face format programs for the delivery of health education [36]. Correspondence format programs include telephone, internet, CD-ROM, and mail formats. The printed format may be particularly advantageous as the material is more likely to be read, saved, and perceived as personally relevant than information presented on a CD-ROM [37, 38]. Even though telephone programs are more personal and immediate and involve more natural language than mail programs [39], both telephone and mail programs are effective in reducing the health risk status of participants [40]. Mail programs place fewer time constraints on people and are more readily available than internet programs [39]. Mail format, which is easily available, is therefore considered suitable for maintaining compliance with preventive interventions for potentially high-risk relatives.

To provide effective lifestyle interventions, medical professionals should comprehensively assess subjects and deliver individualized information, which can be achieved efficiently using computer-tailored health education [41, 42]. Computer-tailored lifestyle intervention is a promising health education technique, particularly for (printed) nutrition education [43] and is well suited to modification of complex health-related behaviors (e.g., by providing feedback). Previous studies have shown that computer-tailored intervention involving questionnaires and tailored messages can result in behavioral changes and weight loss in healthy people [44–46]. Furthermore, computer-tailored interventions have emerged as a new and cost-effective type of health promotion program because they enable personalization of health education without the high cost of personal counseling [43]. The computerized behavioral program is therefore expected to be an effective and feasible intervention tool.

 The objective of this parallel, three-group trial is to investigate the effects of printed computer-tailored lifestyle intervention on favorable lifestyle change, and the effects of genetic counseling about prevention and hereditary risk of type 2 diabetes on the compliance to the life style intervention.

## 2. Methods

### 2.1. Design

This study is a parallel, three-group, randomized, controlled trial investigating the effects of printed computer-tailored lifestyle intervention (LI) on favorable lifestyle change, and the effects of genetic counseling (GC) about prevention and hereditary risk of type 2 diabetes on the compliance to the life style intervention.

Data collected at preintervention, immediately post-GC (baseline), and at 1 week and 3, 6, and 12 months post-GC will be analyzed. The design, conduct, and reporting of the study adhere to the Consolidated Standards of Reporting Trials (CONSORT) guidelines [47].

### 2.2. Subjects

#### 2.2.1. Eligibility Criteria

Subjects were included if they had a first-degree relative with type 2 diabetes and were aged 30–60 years. Those who were already diagnosed with type 2 diabetes or metabolic syndrome, or were already receiving lifestyle intervention, were excluded.

#### 2.2.2. Setting

Subject recruitment was carried out in the medical checkup department of a general hospital in Tokyo.

### 2.3. Interventions

Subjects were randomized into three groups: genetic counseling and lifestyle intervention (GC&LI), lifestyle intervention (LI), and control.

#### 2.3.1. Genetic Counseling

After written consent was obtained, subjects underwent genetic counseling with a certified genetic counselor. The counseling session used the booklet developed by the authors, which has been described elsewhere [48]. Briefly, the booklet consists of four sections, each reflecting a core element of the health belief model, with the following information provided in each section. (1) *Perceived seriousness.* Information on the symptoms and complications of diabetes. (2) *Perceived susceptibility.* Information on the drastic increase in the number of diabetic patients, and the implications of genetic-environmental interactions. Causes of diabetes, such as genetic predisposition, high-fat foods, and/or a sedentary lifestyle [11, 49]. Information on genetic predisposition, decreased insulin secretion, and the decreased insulin sensitivity caused by a high-fat meal [21]. Advice that individuals with an affected first-degree relative have a 2.3–5.5-fold higher risk of developing type 2 diabetes [19] since such individuals seem to have similar genetic predisposition and lifestyle. (3) *Perceived benefits.* Advice that the risk of acquiring diabetes can be modified by a low-fat diet and increased physical activity (PA) [50, 51]. (4) *Perceived barriers.* A summary of concrete methods to modify diet and PA, and a recommendation to refer to professionals for individualized prevention [50, 51]. The total time for the counseling session was approximately 10 min.

#### 2.3.2. Printed, Computer-Tailored Lifestyle Intervention

Lifestyle intervention in this study features tailored and concrete lifestyle recommendations in a computer-based, non-face-to-face format. The intervention will use Lifestyle Intervention Support Software for Diabetes Prevention (LISS-DP). Contents of LISS-DP are developed based on lifestyle intervention protocol for secondary or tertiary prevention in type 2 diabetes patients, which has been developed by one of authors [52, 53].

The intervention strategy consists of the following processes: (1) lifestyle and background data collection by self-administered questionnaire; (2) generation of tailored recommendations; (3) output of tailored recommendations; (4) delivery of the recommendations via mail.

(1) Lifestyle and Background Data Collection by Self-Administered QuestionnaireLISS-DP requires information about the subject's current diet and PA to identify risky or favorable behavior. Current lifestyle behaviors will be assessed using a self-administered questionnaire. The questionnaire is based on two measurement scales: evaluation scale for self-management behavior related to physical activity of type 2 diabetic patients (ES-SMBPA-2D) [54] and Dietary Self-Management Behavior Questionnaire (DSBQ) [55]; which were developed by the authors. These scales measure dietary and PA self-management behaviors in diabetic patients and consist of 32 and 91 items, respectively. We modified these scales to assess preventive dietary and PA behaviors in healthy relatives of patients with type 2 diabetes. Items were chosen for each scale according to the following criteria: dietary behavior shown in previous research to have a significant relationship with total energy intake [52, 53], PA behavior shown to have a significant relationship with energy expenditure [54], and important preventive behaviors as judged by an expert panel. As a result, a lifestyle assessment questionnaire consisting of 53 items was developed, with 15 items assessing “recommended dietary behaviors (RD)” (Table 1), 21 items assessing “recommended physical activity behaviors (RP)” (Table 2), 16 items assessing “nonrecommended dietary behaviors (ND)” (Table 3), and a single item assessing “nonrecommended physical activity behavior (NP)” (Table 3). Questionnaires ask the subjects to indicate the frequency of each behavior on five-point scale which will be converted to a numerical score: never (0), rarely (1), sometimes (2), often (3), or always (4).

(2) Generation of Tailored RecommendationsLISS-DP will be used to assess each subject's lifestyle behaviors and generate individualized recommendations according to the following algorithms (Figure 2). First, subjects will be divided into four groups according to their combination of risk factors, sex, and physical activity level: male/high-PA group (A), male/low-PA group (B), female/high-PA group (C), and female/low-PA group (D). A high physical activity level is defined according to the national health promotion policy (Healthy Japan 21) as ≥30 min of moderate physical activity ≥2 days/week. LISS-DP will then select the items to be assessed in each risk group. In addition to these selected items, subjects with obesity-related risk factors, high BMI, and/or large waist circumference will be assessed using items which have a relationship with obesity. Cut-off point for each obesity-related risk factor was set based on those of national screening program (SHC, mentioned previously). If subjects answer “never” or “rarely” to one of the selected RD or RP items, that item will be identified as a behavior which the subject should aim for. If subjects answer “often” or “always” to one of the selected ND, that item will be identified as a behavior which the subject should refrain from. If subjects answer “always” to NP item, it will be also identified as a behavior which the subject should refrain from. Additionally, if subjects answer “often” or “always” to one of the RD or RP items, that item will be identified as a behavior which should be continued.

(3) Output of Tailored RecommendationsDietary and PA behaviors which should be aimed for, refrained from, or continued by the subject will be printed on a lifestyle advice sheet consisting of computer-based lifestyle recommendations and a free-comment section for use by the clinical diabetes educator.The lifestyle recommendations consist of five sections. Sections I and II provide positive feedback about favorable behaviors to increase self-awareness about preventive behaviors. RD item(s) and RP item(s) identified as behavior(s) which should be continued will be indicated as follows.Section IYour current behaviors(s) shown below are effective for maintaining a favorable total energy intake. Be confident in continuing these actions.
Section IIYour current behavior(s) shown below are effective for maintaining a favorable physical activity level. Be confident in continuing these actions.
Dietary behavior(s) which should be aimed for will be identified in section III as follows.Section IIIThe behavior(s) shown below are recommended for maintaining a favorable total energy intake. Please incorporate these into your daily life to achieve favorable dietary habits.
Both dietary and PA behavior(s) which the subject should refrain from will be identified in section IV as follows. Section IVThe behavior(s) shown below would cause an excess of calorie intake. Please refrain from these behaviors.
Physical activity behavior(s) which should be aimed for will be identified in section V as follows. Section VThe behavior(s) shown below are recommended for increasing physical activity. Please incorporate these into your daily life to achieve favorable physical activity levels.
Following the lifestyle recommendations, a clinical diabetes educator will write advisory comments. The advisory comments will mention general recommendations for lifestyle change, and integrate the individual recommendations. After the second intervention, changes in lifestyle since the previous data collection will be also be shown in the advisory comments. 

(4) Delivery of Recommendations via MailThe lifestyle advice sheet will be sent to subjects via mail.

#### 2.3.3. Control Group

Subjects allocated to the control group will receive conventional routine care during the study period, including disclosure of medical checkup results and general information about diabetes prevention. This conventional routine care will also be provided to the other two groups. The genetic counseling booklet and three lifestyle advice sheets will be sent to subjects in the control group after the end of the study period.

### 2.4. Primary Outcomes

#### 2.4.1. Changes in Total Energy Intake, Fat-Energy Ratio, and Physical Activity

The primary outcomes of this study are changes in total energy intake, fat-energy ratio, and physical activity levels between baseline and the end of the intervention period. These variables will be measured by self-administered questionnaires. The questionnaires include a dietary measurement scale (Modified-Ministry of Health and Welfare-Food Questionnaire (M-MHW-FQ)) and a physical activity scale (International Physical Activity Questionnaire (IPAQ)). The M-MHW-FQ has been shown to be a reliable method of calculating energy intake and fat-energy ratio [56]. The IPAQ has been shown to be a valid method of assessing physical activity across various life activities, including during leisure activities [57–59].

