### 2.7. Sample Size

We had conducted preliminary intervention study for offspring of type 2 diabetes patient [24]. The intervention in preliminary study was conducted in mail-delivered style, similar to current study, while advice sheet was made by a dietician and a medical fitness therapist in handwriting. After three-times intervention during 6 months, −1.0 SD change was observed in primary outcome (total energy intake). Intervention in current study is computer-based, it means less tailored to individual participant than preliminary study. So observed effect in this study is expected to be modest compared to preliminary study. We calculated the necessary sample size to be 64 per study arm to detect a moderate effect size (0.5 SD), with 80% power at the 5% significance level. Assuming a dropout rate of 10% from the results of a previous similar study [37, 46], 72 participants are needed for each arm.

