### 2.11. Statistical Analysis

Statistical analysis will be carried out on an intention-to-treat basis. We will summarize continuous variables using means and standard deviations, and categorical variables using counts and percentages.

The effects of GC will be investigated by comparing the GC&LI and LI groups. Similarly, the effects of LI will be investigated by comparing the LI and control groups. Primary outcomes will be analyzed by ANCOVA, adjusting for baseline values. Differences between groups in secondary outcomes at each assessment point will be analyzed by the Student's *t*-test for continuous variables or the Mann-Whitney *U* test for ordinal variables.

In all tests, a *P* value of <0.05 by two-tailed test will be considered significant. Analysis will be performed using SAS 9.2 (SAS Institute, Cary, NC, USA) software for windows.

All study protocols have been approved by the institutional review board of the School of Medicine, The University of Tokyo and Social Insurance Chuo General Hospital. Clinical Trial Registration: UMIN-CTR: UMIN00003589, UMIN00003636.

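### Three unranked primary outcomes are each tested at the full 5% in both contrasts with no ordering or adjustment, and the sample size makes no allowance for it

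*Protocol article*

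**What the plan says.** Four statements in the protocol article bear on this.

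- **Outcomes (section 2.4.1).** "The primary outcomes of this study are changes in total energy intake, fat-energy ratio, and physical activity levels". Each change runs from baseline to the close of the intervention. The three stand side by side, with no order and no rule on whether one or all must succeed.
- **Contrasts (section 2.11).** "The effects of GC will be investigated by comparing the GC&LI and LI groups", and "the effects of LI will be investigated by comparing the LI and control groups".
- **Analysis and decision rule (section 2.11).** The method is given as "Primary outcomes will be analyzed by ANCOVA, adjusting for baseline values". The threshold is given as "In all tests, a *P* value of <0.05 by two-tailed test will be considered significant".
- **Sample size (section 2.7).** 64 per arm for a 0.5 SD effect with 80% power at 5%, raised to 72 for 10% dropout. The expected effect is argued down from a preliminary study in which a −1.0 SD "change was observed in primary outcome (total energy intake"). The calculation is in SD units and does not say which of this trial's outcomes it serves.

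**The concern.** Three outcomes in each of two contrasts make six primary tests, each of which may be called significant at 5%. Because the article does not say what counts as success, one favourable outcome out of three could be reported as a positive primary result for lifestyle intervention, or for genetic counseling. That false-positive risk is well above 5%.

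This is not a detail simply left to an analysis plan. The article states its decision rule and applies it to all tests, and it gives a sample size that fits only a single test. The reader cannot tell what the 5% and the 80% refer to.

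**Working it through.** **Inputs.** Three primary outcomes (2.4.1); two contrasts sharing the LI arm, two-sided 0.05 for every test (2.11); 0.5 SD, 80% power, 5%, 10% dropout, 64 and 72 per arm (2.7); equal allocation (2.8). The article does not give correlations between outcomes, so 0 to 0.8 is an assumed range.

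**1. The plan's own figure.** Normal approximation: n = 2(1.960 + 0.842)²/0.5² = 62.8, so 63. The two-sample t-test solution is 63.77, so 64 per arm. Dropout: 64/0.9 = 71.1, so 72. The stated figures are correct, for one outcome in one two-arm comparison at the full two-sided 0.05.

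**2. Chance of at least one false-positive primary result, no true effects.** With independent tests:

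- three tests: 1 − 0.95³ = 14.3%
- six tests: 1 − 0.95⁶ = 26.5%

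The six tests are not independent, because the LI arm enters both contrasts. A simulation (500,000 draws) with that shared arm gives:

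| Assumed outcome correlation | Three outcomes, one contrast | Six tests, both contrasts |
|---|---|---|
| 0 | 14.2% | 24.7% |
| 0.3 | 13.6% | 23.7% |
| 0.5 | 12.5% | 22.0% |
| 0.8 | 9.8% | 17.3% |

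Within one contrast the error is two to three times nominal (9.8/5 = 2.0; 14.2/5 = 2.8).

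**3. If all three outcomes must succeed.** Error does not inflate. With 0.5 SD on each outcome and 64 per arm, each test has mean 0.5/√(2/64) = 2.83 and power of about 80.7% (normal approximation). Power for all three is 0.807³ = 53% at correlation 0, then 58%, 62% and 70% at 0.3, 0.5 and 0.8.

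**4. If alpha is split within a contrast.** At 0.05/3 = 0.0167, t-test power at 64 per arm is 66%. Keeping 80% would need 86 per arm, or 96 with dropout (86/0.9 = 95.6).

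This ignores the gain from baseline-adjusted ANCOVA. With an assumed baseline correlation of 0.5, the effective effect is 0.5/√(1 − 0.25) = 0.577 and the test mean is 0.577 × √32 = 3.27. The critical value is 2.39, so power is Φ(0.87), about 80%.

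**5. If one outcome leads.** With total energy intake tested first at 5% in each contrast, step 1 applies unchanged and 64/72 per arm stands for that outcome.

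**The case against.** The case on the other side has several parts.

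- **A reader might infer that section 2.7 makes total energy intake this trial's single primary outcome and so contradicts section 2.4.1.** The text does not support that. The words about total energy intake describe the preliminary study, and 0.5 SD is not tied to any outcome. The same 64 per arm gives 80% power for any one of the three outcomes with that effect. Section 2.7 suggests a lead outcome but does not declare one.
- **A reader might infer an error rate of about five times nominal.** That needs both contrasts pooled and near-zero correlation. Section 2.1 gives the contrasts separate objectives (lifestyle change for LI, compliance for GC), so adjustment across them is arguable. Energy intake and fat-energy ratio also come from the same food questionnaire, so zero correlation is a poor anchor. The figure per contrast is the safer one.
- **The article never says that any one outcome suffices.** True, and an all-must-succeed rule would not inflate error. But it does not state that rule either, and power would then miss the stated 80%.
- **A 0.05 threshold for each test is compatible with a fixed sequence, which a fuller document might contain.** The threshold alone is compatible. Calling all tests significant at 0.05 is not, because in a sequence the later tests lose that label once an earlier one fails.
- **The end of the intervention period is not tied in the text to the 3-, 6- or 12-month assessment.** Figure 1 is not shown and may settle this, so it carries no weight here.

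**Conclusion.** The point stands within each contrast. With three unranked primary outcomes and 0.05 for every test, the chance of at least one false-positive primary result is about 10–14% instead of 5%, for an assumed outcome correlation of 0.8 to 0. Across both contrasts it is about 17–25%, but controlling that larger figure is a matter of choice.

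The sample size arithmetic is right. What is missing is an allowance for more than one test. Under an any-one reading the error rate is too high; under an all-three reading the power is about 53–70%, assuming 0.5 SD on each outcome. Under neither reading do sections 2.4.1, 2.7 and 2.11 together deliver 5% and 80%.

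**What to change.** Before outcome data are examined, amend sections 2.4.1 and 2.11 so that error is controlled within each contrast, by one of two routes:

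1. **Fixed sequence.** Name total energy intake as lead outcome, then test fat-energy ratio and then physical activity, each at 5% and only if the step before succeeded. The 64/72 per arm stands.
2. **Holm over three primary outcomes.** Restate the power in section 2.7: about 66% at 64 per arm at the smallest step (0.05/3) without baseline adjustment, or about 80% if a baseline correlation of 0.5 is assumed and stated.

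Reserve the label of significance for primary claims to the chosen procedure. State whether the two contrasts are separate families; adjustment across them is optional.

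Neither route needs more participants if the restated power is accepted, but this is more than rewording. Randomization is complete and the trial is registered, so the change must be recorded as a dated post-randomization amendment.

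Each route has a cost. In the sequence, the later outcomes cannot be claimed if energy intake fails, and the Discussion (section 4) notes that mean baseline intake (29.8 kcal/kg/day) already lies in a favorable range, which may leave the lead outcome little room to improve. Under Holm, power per outcome is lower.
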